## Abstract

Preliminary data have shown that it is possible to attempt in vitro fertilization (IVF) treatment in fresh cycles without the use of a gonadotropin-releasing hormone (GnRH) antagonist or any other medication to prevent the luteinizing hormone (LH) surge during ovarian stimulation. To date, there is no information on this topic in the context of a prospective controlled trial. However, as prevention of the LH surge is an established procedure in fresh cycles, the question is whether such a study can be performed in frozen cycles. We aim to perform a pilot study in order to compare the efficacy of a protocol using FSH alone with that of a protocol using follicle-stimulating hormone (FSH) plus a GnRH antagonist for controlled ovarian hyperstimulation (COH) in cycles of elective freezing in the context of a donor/recipient program. This is a seven-center, two-arm prospective pilot cohort study conducted at the respective Assisted Reproductive Units in Greece. The hypothesis to be tested is that an ovarian stimulation protocol that includes FSH alone without any LH surge prevention regimens is not inferior to a protocol including FSH plus a GnRH antagonist in terms of the clinical outcome in a donor/recipient model. The results of the present study are expected to show whether the addition of the GnRH antagonist is necessary in terms of the frequency of LH secretory peaks and progesterone elevations >1 ng/mL during the administration of the GnRH antagonist according to the adopted frequency of blood sampling in all Units.

## 1. Introduction

It is known that during controlled ovarian stimulation (COH) with follicle-stimulating hormone (FSH) for in vitro fertilization (IVF), the positive feedback mechanism can be activated by estradiol, before the follicle is fully matured, leading to the occurrence of a premature luteinizing hormone (LH) surge, which is the main responsible factor for premature luteinization. To prevent a premature LH surge, gonadotropin-releasing hormone (GnRH) agonists and antagonists are routinely used in COH protocols with FSH [1].

Existing data have shown high efficacy of the GnRH agonists in the prevention of LH surges [2,3], whereas the currently used GnRH antagonists have been less effective in controlling pituitary LH secretion. In specific contexts, various studies have reported multiple LH secretory peaks during the administration of a GnRH antagonist at a frequency ranging from 8–35%, with a concomitant rise in progesterone levels in several cases [4,5,6,7,8]. In addition, the GnRH antagonist, ganirelix, at a dose of 0.25 mg per day for 5 days, has been unable to block the positive feedback effect of exogenous estradiol in experiments performed in normal female volunteers during the follicular phase of their menstrual cycle [9]. Furthermore, a previous study has shown that after the administration of one dose of 0.25 mg of the GnRH antagonist, cetrorelix, secretory LH pulses were eliminated for about 6 h, but then a gradual recovery of the pituitary was observed, with a re-establishment of the normal pattern of LH pulses during the last 6 h before the administration of the next dose [10]. This indicates that with the current protocols of daily administration of the GnRH antagonists during COH, there is a period between two successive doses of the antagonist during which the anterior pituitary is not protected against the high levels of the circulating estradiol, which can activate the positive feedback mechanism and the occurrence of LH secretory peaks. Finally, GnRH antagonists do not appear to reduce the basal levels of LH when administered either during COH or in the follicular phase of a normal menstrual cycle [6,9,11]. Notably, during COH with FSH, the administration of a GnRH antagonist begins on day 6 of the treatment cycle, i.e., at a time when blood levels of LH are already significantly reduced due to the increased activity of the negative feedback mechanism from the rising estradiol levels; thus, at that point, the addition of the GnRH antagonist cannot cause a further decrease [6,9] and, probably, is therefore not necessary.

Despite the above-mentioned “weaknesses” of the GnRH antagonists, no significant difference in live birth rate has been shown between COH protocols for IVF using agonists and those using antagonists [12]. This could be interpreted as indicating that any premature rise in LH or even progesterone levels during COH is of negligible value for a successful final outcome. In other words, failure to administer a drug to block the LH surge in IVF cycles may not have a significant impact on the clinical outcome. Preliminary data have shown that it is possible to attempt an IVF treatment in fresh cycles without the use of a GnRH antagonist or any other medication to prevent a LH surge during COH [13]. It was interesting that women receiving a GnRH antagonist had LH levels during stimulation similar or even significantly higher than women without an antagonist [13]. To date, there is no information on this topic in the context of a prospective controlled trial. However, as the prevention of the LH surge is an established procedure in fresh cycles, the question is whether such a study can be performed in frozen cycles.

Recently, progesterone-primed protocols have been introduced in cycles with “freeze all” embryos [14]. The results have shown that the live birth rate following frozen/thawed embryo transfer does not differ significantly between protocols with progesterone and those with GnRH antagonists or agonists, while there is no difference in the congenital malformation risk either [15,16]. This could lead to the safe conclusion that, in the case of elective freezing, GnRH analogues are not necessary for LH surge prevention, while GnRH agonists could be used for triggering the final oocyte maturation. On the other hand, premature luteinization has been shown to reduce the chance of pregnancy in fresh but not in frozen cycles, thus suggesting that progesterone adversely affects the endometrium, which is not a concern in frozen cycles [17]. If so, then it is questionable whether exogenous progesterone is also necessary to prevent the LH surge in elective freezing cycles [18].

The aim of this pilot study is to compare the efficacy of a protocol using FSH alone with that of a protocol using FSH plus a GnRH antagonist for COH in cycles of elective freezing in the context of a donor/recipient program. The hypothesis to be tested is that a COH protocol that includes FSH alone without any LH surge prevention regimens is not inferior to a protocol including FSH plus a GnRH antagonist in terms of clinical outcomes.

## 2. Materials and Methods

### 2.1. Study Design

This is a seven-center, two-arm prospective pilot cohort study to be conducted at the Assisted Reproductive Units of:a.The Department of Obstetrics and Gynecology, Faculty of Medicine, School of Health Sciences, University of Thessaly, Larissa, Greece;b.The Assisted Reproduction Unit, Second Department of Obstetrics and Gynecology, “Aretaieion” Hospital, Medical School, National and Kapodistrian University of Athens, Athens, Greece;c.HYGEIA IVF—Embryogenesis A.R.T. Unit, Athens, Greece;d.The Institute of Fertility, Athens, Greece;e.The Embryolab IVF Unit, Thessaloniki, Greece;f.The Mitosis IVF Centre, Pireaus, Greece;g.The Assisting Nature IVF Unit, Thessaloniki, Greece.

The first two University Units will offer scientific and academic support, while in the rest, the five private Units, the recruitment of the study subjects will take place.

Patients will be recruited from the acceptance of the protocol from the Scientific Committees of all Units. The study protocol has been registered prospectively in clinicaltrials.gov (NCT05759871).

### 2.2. Eligibility Criteria

The inclusion criteria of the study population are: healthy women between 21–32 years old with a BMI of 21 to 29 kg/m^2^ who wish to donate their oocytes; normal ovarian reserve tests; normal menstrual cycles of 26–32 days; absence of any hormonal treatment during the last three months before entering the study and absence of coagulation and/or autoimmune disorders.

The exclusion criteria include: use of other protocols towards oocyte retrieval, such as natural, or modified natural cycles; poor ovarian response according to the Bologna criteria [19]; history of endocrine or metabolic disorders, ovarian cystectomy or oophorectomy; women with a diagnosis of polycystic ovary syndrome; clinical and/or laboratory markers of hereditary or acquired thrombophilia that complied to the standard protocols of each Unit and non-hormonal medication for a serious medical condition.

### 2.3. Participants—Recruitment

For this study, female donors participating in a donor/recipient program will be recruited following a detailed explanation of the study protocol. The selection will be based on the eligibility criteria. All participants will sign a written informed consent before entering the trial. The women will be divided into two groups, i.e., group 1 (study) and group 2 (control). The allocation of patients will be achieved using a 1:1 proportional pattern, depending on the random order in which they enter each Unit. Notably, both patients and gynecologists will be aware of the study protocol used.

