#### 2.4.2. Endometrium Preparation

In recipients, there will be no fresh but only frozen/thawed embryo transfer. For this purpose, their endometrium will be prepared by administering hormone replacement therapy. The women will receive oral estradiol valerate as follows: 2 mg on cycle days 2–3, 4 mg on days 4–5 and 6 mg from day 6 onwards. Once the endometrium, at least 10 days after starting estradiol treatment, becomes thicker than 8 mm in diameter as assessed via a transvaginal ultrasound scan, micronized progesterone (Utrogestan caps 200 mg, Faran A.B.E.E., Athens, Greece) will be given vaginally at the daily dose of 400 mg (200 mg two times per day) or progesterone (Vasclor vag. Gel 8%, 22.5 G, Verisfield U.K. Ltd., Athens, Greece) once daily depending on the participating unit’s protocol. Estradiol valerate administration will continue at a dose of 4 mg per day. The maximum number of embryos to be transferred will be 2 per patient.

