### 2.5. Intended Comparisons and Outcomes

The primary outcome measures will be the frequency of LH secretory peaks during the administration of the GnRH antagonist according to the adopted frequency of blood sampling. A secretory peak of LH is defined as the increase at levels ≥ 10 IU/L. Progesterone elevation > 1 ng/mL any time during the ovarian stimulation period will be also evaluated. Secondary outcome measures will be ongoing clinical pregnancy (fetal heartbeat at ultrasound) and miscarriage rates. Other prespecified outcome parameters included the total dose of gonadotropins (FSH), the endometrial thickness at day of triggering, number of retrieved cumulus oocytes complexes (COCs), MII oocytes, transferred embryos, day of embryo transfer, biochemical pregnancy (positive β-hCG), multiple pregnancy, ectopic pregnancy and live birth rates. Maternal side effects from the use of both drugs will also be monitored, including ovarian hyperstimulation syndrome. Embryo quality for embryo transfer or cryopreservation will be assessed according to morphological criteria [20].

Our primary analysis will be performed to provide a direct comparison of the study and control groups. We will also carry out logistic regression analysis, inserting variables, including demographic and IVF cycle characteristics, in order to reveal potential independent predictors that could potentially contribute to the change in the primary outcomes and live birth rate.

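### Only donors are selected and allocated, but the secondary clinical outcomes arise in recipients, and nothing stated keeps the donor–recipient match independent of the donor's group

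*Protocol article*

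**What the plan says.** **Who is selected and allocated.** Section 2.2 of the protocol article admits "healthy women between 21–32 years old with a BMI of 21 to 29 kg/m^2^ who wish to donate their oocytes". Section 2.3 says that "female donors participating in a donor/recipient program will be recruited following a detailed explanation of the study protocol", and these women are then divided 1:1 by order of entry at each unit. It adds that "both patients and gynecologists will be aware of the study protocol used".

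**What is to be shown.** The Introduction states the hypothesis that FSH alone "is not inferior to a protocol including FSH plus a GnRH antagonist in terms of clinical outcomes". The Abstract frames it "in terms of the clinical outcome in a donor/recipient model", and the Discussion repeats the aim as similar efficacy after frozen/thawed transfer.

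**Where clinical outcome arises.** Section 2.4.2 states: "In recipients, there will be no fresh but only frozen/thawed embryo transfer". It then gives the endometrial preparation, leaves the progesterone product to the unit, and sets a ceiling: "The maximum number of embryos to be transferred will be 2 per patient".

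**Outcomes and analysis.** In 2.5 the primary outcome is the frequency of LH peaks, and progesterone above 1 ng/mL is evaluated alongside it. "Secondary outcome measures will be ongoing clinical pregnancy (fetal heartbeat at ultrasound) and miscarriage rates"; live birth is listed among the further outcomes. The main analysis compares the two groups directly. Logistic regression is added to look for predictors, using demographic and cycle variables without saying whether they belong to the donor or the recipient.

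**The concern.** Allocating donors can at best balance donors. Pregnancy, miscarriage and live birth also depend on the woman who receives the embryos, and she enters by a second step, the match, for which the article states no rule. Because all embryos are frozen, transfer takes place after the donor's group is known. Whoever makes the match, or decides between one and two embryos, may therefore know the group.

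If that knowledge influences either decision, recipient prognosis or the number of embryos will differ between groups. The clinical comparison would then mix the effect of stimulation with the effect of recipient selection. In a non-inferiority comparison this can go either way: it can hide a real deficit or create an apparent one.

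**Working it through.** **1. Population against outcome**

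| Item | Donor | Recipient |
|---|---|---|
| Eligibility (2.2) | full list | none stated |
| Recruitment and 1:1 allocation (2.3) | yes | none stated |
| LH peaks, progesterone elevation (2.5) | measured here | – |
| Pregnancy, miscarriage, live birth (2.5) | – | arise here |
| Rule linking donor to recipient | none stated | none stated |
| Covariates named for adjustment (2.5, 2.7) | not specified whose | not specified whose |

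The primary outcomes stay within the allocated population. The clinical outcomes do not.

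**2. The plan's own figure**

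Inputs from 2.6: 20% experimental, 15% control, margin 10 points, one-sided 5%, power 80%.

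n per group = (1.645 + 0.842)² × (0.15×0.85 + 0.20×0.80) / (0.10 + 0.05)² = 6.18 × 0.2875 / 0.0225 ≈ 79.

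That gives 158 in total against the stated 160, so the figure reproduces and is not in dispute. Power at 80 per group is 80.4%. Section 2.6 does not name the outcome behind 20% and 15%; treating it as a recipient outcome such as pregnancy is an assumption, used only in step 3.

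**3. What a recipient imbalance would do**

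Let b be the shift in the observed experimental rate that comes only from recipient prognosis. The document gives no value, so b is assumed.

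Probability of declaring non-inferiority = Φ[(0.10 + p_E + b − p_C)/SE − 1.645], where SE = √{[p_C(1−p_C) + (p_E+b)(1−p_E−b)]/n} and n = 80.

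| Scenario | b = 0 | 2.5 points | 5 points |
|---|---|---|---|
| False non-inferiority, true 15% vs 5%, b favouring FSH alone | 5.0% | 12.7% | 24.6% |
| False non-inferiority, true 25% vs 15%, b favouring FSH alone | 5.0% | 10.4% | 18.8% |
| Power, true 15% vs 20%, b against FSH alone | 80.4% | 69.1% | 55.0% |

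(Control rate is given first.) Example, first row, b = 5 points: SE = √[(0.1275 + 0.09)/80] = 0.0521; (0.10 + 0.10 − 0.15)/0.0521 = 0.959; Φ(0.959 − 1.645) = 24.6%.

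At the pilot size of 25 per group, a 5-point shift favouring FSH alone raises false non-inferiority from 5% to between 11.1% and 13.4%. Power without any bias is only 40.3%.

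**4. How large b might be**

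Roughly, b = (imbalance in favourable recipients) × (pregnancy-rate gap between favourable and unfavourable recipients). With an assumed imbalance of 20 to 40 points and an assumed gap of 10 to 20 points:

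- low end: 0.20 × 0.10 = 2 points
- high end: 0.40 × 0.20 = 8 points

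Both factors are assumptions, so the range shows scale and is not an estimate.

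**5. Chance alone**

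With 25 per group, one recipient per donor (not stated) and a trait present in half of recipients, the standard error of the between-group difference is √(2 × 0.25/25) = 14 points. A 20-point imbalance (5 of 25) is 1.4 standard errors. It would not by itself show arm-driven matching, but an unadjusted comparison would leave it uncorrected.

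**The case against.** The best defence is that this is a condensed article about a pilot. The primary outcomes are donor measurements, and the Abstract says the results should show whether the antagonist is needed in terms of LH peaks and progesterone. Recipient entry rules and matching may stand in the full protocol or in each unit's practice. The embryo ceiling and the morphological grading are stated without distinction by group. The number of embryos transferred is a listed outcome, so a difference would be visible. Regression is planned for pregnancy, miscarriage and live birth. The Discussion concedes observational bias, disclaims a definite conclusion and looks ahead to a randomised trial.

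Much of this stands, and it rules out several stronger readings:

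- A reader might infer that recipients are unselected. The article only fails to state criteria; units may apply their own.
- A reader might infer that matching is done by people who know the group. The article does not say who matches or when. Open allocation with no matching rule makes this possible, not established.
- A reader might take the fear of premature LH surges and ovulation, reported in the Discussion, as evidence of steering. It was met while recruiting centres and does not describe how the participating units behave.
- A reader might conclude that separate recipient consent is missing. Section 2.3 requires consent from all participants, and the article does not show that recipients are left out.

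What the defence does not answer is the structure of the comparison. The article itself rests a non-inferiority hypothesis on clinical outcome, states that the study is open, and makes the direct comparison its main analysis. The regression is framed as a search for predictors and names no recipient covariate. The general admission of bias neither identifies nor limits this source. An analysis plan written later cannot conceal a match already made.

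**Conclusion.** The point holds for the secondary clinical comparison and not for the primary outcomes. As written, allocating donors does not protect the pregnancy, miscarriage and live-birth comparison from differences between recipients, and the main analysis does not correct for them.

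The document gives no figure for the size of the bias. An assumed 5-point shift is half of the 10-point margin in 2.6. At 80 per group it would raise the false non-inferiority rate from 5% to about 19–25%, or cut power from 80% to 55%, depending on direction. These figures rest on the assumed shift, on reading the unnamed outcome in 2.6 as a recipient outcome, and on a normal approximation. They do not show that such a shift will occur. The sample size itself is correct on its stated inputs.

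The change is worth making now because it is cheap and because the pilot is meant to lead to a randomised trial that would inherit the same gap.

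**What to change.** **Section 2.3.** Fix and log the donor–recipient match before the donor's group is assigned. Where the match must come later, have it made by staff who do not know the group. If the 1:1 pattern by order of entry makes the next group foreseeable, a log alone will not conceal it, and the second route is safer. State that each unit's existing recipient criteria, and its rule for choosing one or two embryos, apply identically in both groups. No new recipient exclusions are needed for this purpose, and the embryo rule itself is for the investigators to decide.

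**Sections 2.5 and 2.7.** Prespecify recipient age and number of embryos transferred as recorded variables. Make the pregnancy and live-birth comparison adjusted for recipient age, in place of an unadjusted comparison followed by a predictor search. The number of embryos should be reported by group rather than adjusted for by default, because stimulation may itself affect how many embryos are available.

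**Cost.** A protocol amendment, a match log and some constraint on scheduling. No extra donors or procedures are required.

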Finally, we admit that this is an observational study that will carry the associated biases a priori; as a result, no definite conclusion can be drawn. In contrast, we believe that this is a new theory that has to be proven step-by-step. We fully acknowledge the anxiety of both patients and clinicians for premature LH surges and ovulation; especially for the later, we came across a lot of negative beliefs and fear when we tried to recruit IVF centres for participation. Our further—and initial—aim, though, remains to conduct a proper RCT to prove or disprove the outlined theory, but to do so with some preliminary data in our hands.

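### Donors are allocated 1:1 by order of arrival, which is not randomisation and has no described concealment, yet the plan tests non-inferiority by direct comparison

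*Protocol article*

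**What the plan says.** Section 2.3 gives the allocation rule: "The allocation of patients will be achieved using a 1:1 proportional pattern, depending on the random order in which they enter each Unit". The only random element named is the order in which women arrive. The same section adds that "both patients and gynecologists will be aware of the study protocol used".

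Section 2.1 gives the design: "This is a seven-center, two-arm prospective pilot cohort study". Of the seven units, "The first two University Units will offer scientific and academic support", and recruitment is confined to the other five: "the five private Units, the recruitment of the study subjects will take place".

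Section 2.4.1 then sets the stimulation regimen for each group, so treatment follows from the study's own allocation. The Introduction states a non-inferiority hypothesis. Section 2.6 sizes the study for a 10-point margin (160 women, preceded by a pilot of 50). Section 2.5 makes the direct comparison of the two groups the primary analysis, and Section 2.7 analyses by intention to treat.

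The Discussion concedes: "we admit that this is an observational study that will carry the associated biases a priori". It adds that no firm conclusion will follow and that a proper randomised trial is the further aim, once preliminary data exist. On attitudes to premature surges it reports: "we came across a lot of negative beliefs and fear when we tried to recruit IVF centres for participation".

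**The concern.** The women are split 1:1 by the study and given different regimens as a result. That is prospective assignment of an intervention, whatever the label. What the rule lacks is a sequence that the recruiting unit cannot foresee or influence. Staff have some control over when a donor is consented and scheduled, so they have some control over her place in the order. If they also know how the 1:1 pattern runs, they can match donors to arms.

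This matters because the planned inference relies on comparable groups. Analysis by intention to treat preserves the groups as they were assigned; it cannot repair an assignment that was itself selective. A non-inferiority conclusion is also open to a bias that flatters the new regimen. The Discussion intends the pilot to supply preliminary data for a randomised trial, so a distorted pilot would feed into that decision.

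This is not a missing detail that a fuller protocol might supply. Section 2.3 names the method, and the named method is not random.

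**Working it through.** **1. The plan's own sample size.** Inputs from Section 2.6: control 15%, experimental 20%, margin 10 points, one-sided 5%, power 80%, 1:1. With the unpooled normal approximation,

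n per arm = [0.15×0.85 + 0.20×0.80] × (1.645 + 0.842)² / (0.20 − 0.15 + 0.10)² = 0.2875 × 6.18 / 0.0225 ≈ 79.

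This gives 158 in total against the stated 160, so the figure reproduces. At 80 per group the power is 80.4%. At the pilot's 25 per group, the same inputs give 40.3%. None of this depends on how the 1:1 list is produced, so replacing arrival order with a random list leaves the sample size as it is.

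**2. How guessable the next arm is.** Assumption: 50 donors spread evenly over five units, 10 each (the document gives no target per unit). The recruiter is assumed to see past assignments.

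- Strict alternation: only the first donor is unknown, so the expected share guessed correctly is (0.5 + 9)/10 = 95%. The simulation agrees.
- Permuted blocks within unit, with the recruiter always guessing the arm that is behind: size 4, 68%; sizes 4 and 6, 68%; sizes 2, 4 and 6, 69% (simulated).
- Simple randomisation: 50%.

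Varying the block size among small values therefore does little in units this small.

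**3. What a bias would do to the non-inferiority test (illustration only).** Put the truth at the margin (control 15%, experimental 5%) with 80 per group, and add a bias b in favour of the experimental arm. The one-sided error is Φ(b/SE − 1.645), where SE = √{[0.15×0.85 + p(1 − p)]/80} and p = 0.05 + b.

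- b = 0: 5.0%
- b = 2 points: SE = 0.0491, error 10.8%
- b = 5 points: SE = 0.0521, error 24.6%

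The values of b are assumptions. Section 2.6 does not name its endpoint; the calculation follows its orientation, in which the higher rate is better.

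**4. Whether regression could rescue the comparison.** Sections 2.5 and 2.7 plan logistic regression. If the Section 2.6 rates applied to the pilot, the expected number of events would be 25×0.15 + 25×0.20 = 8.75. About nine events support very little multivariable adjustment, and a recruiter's reason for steering a donor need not be a recorded variable.

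**5. Arm balance under simple randomisation.** With 50 women, the standard deviation of the size of one arm is √(50×0.5×0.5) = 3.5. A 20/30 split would raise the variance factor from 2/25 = 0.080 to 1/20 + 1/30 = 0.083, about 4%.

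**The case against.** The best defence is that the limitation is disclosed and deliberate. The authors call the study observational, disclaim firm conclusions, and place the randomised trial later. That stands as a reason to lower the severity. It does not make the bias unavoidable: the study already controls assignment, and the Introduction and Section 2.6 still state a non-inferiority hypothesis and margin.

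Several stronger readings are tempting, and the document does not support them.

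- *Every next assignment is known.* Section 2.3 does not say how the 1:1 pattern is produced or when the assignment becomes known. Strict alternation is an inference.
- *Clinicians will put low-risk donors in the FSH-only arm.* The Discussion says cycles with a premature surge cannot be predicted, and Section 2.2 narrows the pool to healthy women with normal reserve tests and regular cycles. No variable is given by which staff could pick out donors at low risk of an LH peak, although steering on expected oocyte yield remains conceivable.
- *The reported fear proves a motive.* It was met while approaching centres. The document does not say that staff in the units that joined share it.
- *Everyone is unblinded.* Only patients and gynecologists are named, and an LH peak is defined by a laboratory value of at least 10 IU/L.

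**Conclusion.** The concern holds as a flaw in the stated allocation rule. Arrival order is described as random but is not randomisation, no concealment is described, and the treating gynecologists know the regimen. Selective entry is therefore possible, in a study that assigns treatment itself and compares the arms directly for non-inferiority.

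The possible loss of concealment is large if the pattern is strict alternation: about 95% guessable against 50% under simple randomisation, assuming 10 donors per unit. The direction and size of any effect on outcomes cannot be derived from the document. A reader might multiply, say, 10–30% of donors steered by a risk gap of 10–20 points and arrive at 1–6 points of bias in favour of FSH alone. The document supports neither input nor the direction, and the 10-point margin belongs to the calculation for 160 women, not to the pilot of 50. The illustration in the working shows only that a few points of bias, if present, would matter.

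The authors' own caveat makes this less grave than it would be in a confirmatory trial. It is still worth correcting before recruitment, because the correction is small.

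**What to change.** Replace the allocation sentence in Section 2.3 with a computer-generated 1:1 random allocation that is held centrally, for example by one of the two non-recruiting university units. Release each assignment only after consent and eligibility are recorded, so that a recruiter who guesses the next arm cannot act on it after the donor is entered. Use simple randomisation, or large or varied blocks; small blocks within an open-label unit stay about 68–69% guessable even when their sizes vary. Then describe the study consistently as an open-label randomised pilot, and remove the observational and cohort labels from Section 2.1 and the Discussion.

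If arrival-order allocation is kept, stop calling it random, drop the non-inferiority claim, and report descriptive estimates for each group with their intervals.

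Cost: a protocol amendment, a small central release step, and perhaps slightly unequal arms under simple randomisation. Sample size, sites and treatments do not change. The document gives no cost figure and reports reluctance among centres, so acceptance of random allocation may be the real difficulty; a randomised pilot would at least test it.
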